## Methods

### Design

The study is designed as a two arm randomised controlled non-inferiority trial comparing B-CBT for adult depression to treatment as usual (TAU) with an economic evaluation alongside. The present trial is part of the national project ENTER located and coordinated from the Center for Telepsychiatry and is additionally affiliated with the EU-study E-COMPARED [28].

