### Randomisation and blinding

An independent researcher who is not involved in the trial performs the randomisation (centrally from Amsterdam) at an individual level, stratified by country after eligibility and baseline measurement. A computerised random number generator (Random Allocation Software) will be applied with an allocation ratio of 1:1. Block randomisation will be used with variable block sizes that vary between eight and fourteen allocations per block.

The assessors for eligibility will be blinded to group allocation. During treatment, blinding of participants and clinicians are naturally impossible. Researchers and statisticians involved in the analyses will be blinded to group allocations. The groups will be numbered in the dataset without revealing which treatment was given. The questionnaires administered solely to the B-CBT group will be analysed in a separate dataset.

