## Sample size and statistical analyses

The primary outcome is analysed by regressing the three-month follow-up PHQ-9 data on the baseline PHQ-9 score and a treatment group indicator. We will use an ancova model for this purpose. Missing values are handled using a full-information maximum likelihood estimator. In case of dropout, we will use the last observed values in a supplementary intention-to-treat analysis. Missingness sensitivity will be assessed with a best-/worst-case comparison, where missing values are replaced with the minimum and maximum values observed at follow-up.

The primary hypothesis is that the blended care intervention will be no less effective than the TAU intervention in reducing depression symptoms. A sample size of 130 in two balanced groups will yield a power of at least 80% to detect standardised mean differences above 0.5 on a normally distributed variable. This equivalence interval is slightly narrower than other estimates of minimally clinically important differences [43].

In addition, we will compare the development of PHQ-9 in the two groups using the weekly measurements in a mixed effects model. We will model the individual trajectories as random slopes, and then let the treatment group predict the slopes. Significant slope differences between groups will indicate either faster or slower treatment effects in the blended care group. In case of non-normal data, we will use an appropriate measure of transformation or a generalised linear model. Variables with significant variations between groups at baseline are introduced as control variables.

Secondary outcomes will be analysed using t-tests or a rank sum test. Where appropriate, differences between baseline and follow-up scores are used as outcomes instead of only comparing the follow-up score.

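### In this non-inferiority trial the supplementary intention-to-treat analysis carries the last value forward, which can shrink a true B-CBT deficit and so cannot show that the conclusion is robust

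*Protocol article*

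**What the plan says.** The hypothesis is one of non-inferiority: "The primary hypothesis is that the blended care intervention will be no less effective than the TAU intervention in reducing depression symptoms". The section Sample size and statistical analyses then sets out the following.

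- **Primary analysis.** "The primary outcome is analysed by regressing the three-month follow-up PHQ-9 data on the baseline PHQ-9 score and a treatment group indicator", by ANCOVA, with missing values handled by full-information maximum likelihood (FIML).
- **Supplementary analysis.** "In case of dropout, we will use the last observed values in a supplementary intention-to-treat analysis". No other analysis carries the intention-to-treat label.
- **Sensitivity to missingness.** A best-/worst-case comparison in which "missing values are replaced with the minimum and maximum values observed at follow-up". The text does not say whether one extreme goes into both arms at once or opposite extremes go into the two arms.
- **Weekly data.** PHQ-9 is collected weekly (Table 2). A mixed model compares the weekly slopes, but the weekly scores are not mentioned for handling a missing 3-month score.

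No expected dropout rate is given.

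**The concern.** Carrying a last value forward assumes that a patient's score stays where it was at dropout. On an outcome that falls over treatment, a value from early in treatment comes from a time when the arms have had little chance to differ. Mixing such values into both arms pulls the means together. In a superiority trial that bias is cautious; here it moves the estimate towards the conclusion the trial hopes to reach. The method also counts filled-in values as if they had been observed.

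The article gives reasons to expect dropout that is neither random nor alike in the two arms. Patients who deteriorate may be discontinued (Treatment as usual). Weekly monitoring in the B-CBT arm runs inside the online programme, while the other questionnaires use a separate survey system (Outcome measurements). A B-CBT patient who stops using the programme may therefore stop producing weekly scores, so the timing of the last value could differ by arm.

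At stake is the robustness evidence for the main claim. A supplementary analysis that agrees with the primary result gives little reassurance if it tends to move towards no difference, or if the sign of its bias is unknown.

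**Working it through.** **1. The plan's own figure.** "A sample size of 130 in two balanced groups will yield a power of at least 80% to detect standardised mean differences above 0.5". With 65 per arm, SD 1 and two-sided α 0.05 (an assumption; equivalent to one-sided 0.025), power = Φ(0.5 × √(65/2) − 1.96) = Φ(0.890) = 81.3%. The stated figure reproduces and is not in dispute.

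**2. What FIML does here.** Baseline and group are complete and only the 3-month score is missing. A patient without that score then adds nothing to the estimate of the regression of outcome on baseline and group. The estimate is essentially that of completers, valid if data are missing at random given baseline and arm. Adding the weekly scores as auxiliary variables would change that.

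**3. Assumed inputs (none is in the article).** Baseline mean 15; 3-month completer means 8 (TAU) and 10.5 (B-CBT); SD 5; observed follow-up minimum 0 and maximum 24. The deficit is 10.5 − 8 = 2.5 points, or 0.5 SD, the size used in the sample-size statement.

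**4. Formula.** Estimated deficit = [(1 − d_B) × 10.5 + d_B × x_B] − [(1 − d_T) × 8 + d_T × x_T], where d is the dropout proportion and x the mean imputed value in each arm.

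**5. Carry-forward, equal dropout.** With baseline carried forward, x_B = x_T = 15 and the deficit is (1 − d) × 2.5:

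| d | Deficit |
|---|---|
| 10% | 2.25 |
| 20% | 2.00 |
| 30% | 1.75 |

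If half of each arm's gain had been reached at dropout, x_T = 11.5 and x_B = 12.75. At 20% the deficit is 0.8 × 2.5 + 0.2 × 1.25 = 2.25.

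**6. Carry-forward, unequal dropout (baseline carried forward).**

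- TAU 10%, B-CBT 30%: (7.35 + 4.50) − (7.20 + 1.50) = 3.15, wider than 2.5.
- TAU 30%, B-CBT 10%: (9.45 + 1.50) − (5.60 + 4.50) = 0.85.

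**7. Effect on the confidence limit (20% equal dropout, no baseline adjustment).** Non-inferiority is judged on the upper limit.

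- Completers, 52 per arm: SE = 5 × √(2/52) = 0.981; upper limit 2.5 + 1.96 × 0.981 = 4.42.
- Baseline carried forward, 65 per arm, carried values also with SD 5: the variances are 25 + 0.16 × 7² = 32.84 (TAU) and 25 + 0.16 × 4.5² = 28.24 (B-CBT). SE = √(61.08/65) = 0.969; upper limit 2.00 + 1.96 × 0.969 = 3.90.

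Counting 65 rather than 52 per arm would narrow the interval by 1 − √(52/65) = 11% at unchanged SD. In this example the mixture of values widens the SD and offsets most of that, so the fall in the limit comes mainly from the shifted estimate.

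If 2.5 points is taken as the margin, a true deficit exactly at the margin should be declared non-inferior 2.5% of the time. Under carry-forward from baseline the chance is Φ((2.5 − 1.96 × 0.969 − 2.00)/0.969) = Φ(−1.44), about 7.4%.

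**8. Best-/worst-case check, 20% equal dropout.**

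| Rule | Deficit |
|---|---|
| Minimum in both arms | 2.00 |
| Maximum in both arms | 2.00 |
| Maximum B-CBT, minimum TAU | +6.80 |
| Minimum B-CBT, maximum TAU | −2.80 |

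The same extreme in both arms dilutes the point estimate in both runs, but not always the limit. For the minimum, the variances are 20 + 0.16 × 8² = 30.24 and 20 + 0.16 × 10.5² = 37.64, and the upper limit is 2.00 + 1.96 × √(67.88/65) = 4.00. For the maximum they are 20 + 0.16 × 16² = 60.96 and 20 + 0.16 × 13.5² = 49.16, and the upper limit is 2.00 + 1.96 × √(110.12/65) = 4.55, slightly above the completers' 4.42.

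**The case against.** **The primary analysis is already likelihood-based.** This stands. Carry-forward is supplementary, the primary analysis excludes no randomised patient by rule, and nothing describes it as per-protocol. A reader might infer that the trial has no other analysis of the randomised groups; the article does not support that, since carry-forward is the only intention-to-treat analysis by label alone. If dropout were random, the primary estimate would be unbiased. But FIML as described relies on missing at random given baseline and arm, so any departure has to be explored by the supplementary analyses. The planned mixed model of weekly scores addresses speed of change, not the 3-month comparison.

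**The best-/worst-case check may already be directional.** This also stands. A reader might infer that the same extreme goes into both arms. The article does not say so, and a best-/worst-case comparison can naturally mean opposite extremes, in which case the check includes the adverse bound. Arm assignment is detail that a condensed article may leave to a fuller document, so by itself it would not be a finding. It is worth settling alongside the change to carry-forward.

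**The direction of bias is not fixed.** This is correct. A reader might infer that carry-forward always favours non-inferiority, but with more dropout in B-CBT than in TAU it can widen the deficit (3.15 against 2.5). That does not rescue the method: a check whose bias has unknown sign does not demonstrate robustness.

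**Multiple imputation and tipping-point analyses are good practice, and omitting them is no error.** This is true of omission alone. Here the article commits to a specific weaker method, and the data for a better one are already being collected.

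**Conclusion.** The point holds as a weakness in a stated supplementary method. It is not a flaw in the primary estimator. Carry-forward shrinks a true B-CBT deficit when dropout is similar in the arms, by up to a factor of 1 − d when baseline is the value carried and by less when later values are. It can bias either way when dropout differs, and it treats imputed values as data. At an assumed 20% equal dropout, a 2.5-point deficit becomes 2.00 to 2.25, according to how far patients had progressed.

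The sizes depend on assumed means, SD, dropout rates and dropout timing, and the limits in the working ignore baseline adjustment. The equal-dropout direction needs only that the arms differ less at the last observed value than at 3 months. The change should be made before unblinding; it affects the evidence for robustness rather than the deciding analysis.

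**What to change.** 1. Replace carry-forward with a supplementary analysis of all randomised patients, by likelihood or multiple imputation, that uses the weekly PHQ-9 scores as auxiliary data for a missing 3-month score.
2. Add a delta (tipping-point) analysis that worsens imputed B-CBT values only, in steps, and report the step at which non-inferiority is lost.
3. State the extreme bounds by arm: maximum for missing B-CBT with minimum for missing TAU, and the reverse.

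The cost is revised wording and a little more analysis. The weekly scores are already scheduled, so no new data are needed and the sample size does not change.

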### Treatment as usual (TAU)

TAU will be defined as 12 sessions of face-to-face CBT including the same core components as the B-CBT condition. Additionally, interventions on core beliefs and rumination can be included according to the same criteria as in the B-CBT condition. See Table 1 for an overview of the intervention.

Patients in either condition is monitored weekly for symptoms of depression including suicidal ideation and -intent. Should any participant deteriorate or show signs of suicidal intent, an assessment interview will be conducted and the patient will be discontinued if necessary and referred to relevant treatment.

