### Outcome measurements

Baseline measures will be administered after consent has been granted prior to randomisation. The participants will be followed up three-, six-, and twelve months after baseline measurement. In case of drop-out, a short questionnaire regarding reasons for drop-out will be administered. All questionnaires for the participants will be administered online. A secure web application for building and managing online surveys (RedCap) will be used for all questionnaire packages except the weekly monitoring for the B-CBT group, which will be administered from within the treatment programme. See Table 2 for an overview of measurements and time points. Data is stored by Odense Patient data Exploratory Network. Data is managed by a local data manger with training and prior experience in datamangement. The datamanager quality checks data continuously. Data is collected, transferred, and stored securely electronically and is approved by the Danish Data Protection Agency (J.nr.: 14/26634 Reg. nr.: 2008-58-0035).

**Table 2 Tab2:** Overview of measurements

Variable	Instrument	Items	Time (mins)	Screening Baseline	Weekly	3 months	6 months	12 months
Questions taken from participants								
Demographics		n/a	1	X				
Current treatment		n/a	2	X				
Diagnostic interview	M.I.N.I.	n/a	15	X				X
Depressive symptoms	QIDS-SR16	16	3	X	Item 12	X	X	X
	PHQ-9	9	2	X	X	X	X	X
Treatment preference		1	1	X				
Patient expectancy	CEQ	8	2	X				
Working alliance	WAI-SF	12	3			X		
Technology alliance	TAI-SR^a^	12	3			X		
Client satisfaction	CSQ-8	8	3			X		
Satisfaction with the online programme	SUS^a^	20	3			X		
Drop-out	Number of sessions completed - data extraction	n/a	0				X	
	Patients reason for drop-out. Questionnaire	3	2				X	
Questions taken from therapists								
Working alliance	WAI-SRT	12	3			X		
Satisfaction with the online programme	SUS^b^	20	3			X		

^a^Offered to condition receiving blended treatment only, ^b^Has to be completed once per therapist after completion of the first treatment

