#### Primary outcome

The Patient Health Questionnaire-9 (PHQ-9) [30] will be used as primary outcome measurement to evaluate change in severity of depressive symptoms. It is a nine items questionnaire which can be used to screen and diagnose patients with depressive disorders. The nine items are each scored on a 0–3 point scale with a total score ranging from 0–27 with higher scores indicating more severe depression. The PHQ-9 has been shown to have good psychometric properties [32].

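### The weekly PHQ-9 analysis reads a difference in slope as a difference in speed, but a single slope per patient cannot separate speed from amount and can label the arm that improves sooner as slower

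*Protocol article*

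**What the plan says.** The section Sample size and statistical analyses of the protocol article tests the three-month PHQ-9 by ANCOVA as the primary analysis. As an additional analysis, "we will compare the development of PHQ-9 in the two groups using the weekly measurements in a mixed effects model". The model is described in one sentence: "We will model the individual trajectories as random slopes, and then let the treatment group predict the slopes". The reading of the result is then fixed: "Significant slope differences between groups will indicate either faster or slower treatment effects in the blended care group".

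The section gives no curvature, piecewise or categorical term for time, and does not say whether group may also shift the intercept. Its only stated departure from the default concerns the distribution of the data and not the shape of the time course: "In case of non-normal data, we will use an appropriate measure of transformation or a generalised linear model".

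Weekly data exist in both arms (Treatment as usual (TAU): "Patients in either condition is monitored weekly for symptoms of depression"), and Table 2 lists the PHQ-9 as a weekly measure. On this scale improvement is a fall, with "higher scores indicating more severe depression" (Primary outcome).

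**The concern.** The conclusion drawn is about speed. The quantity tested, if each patient has one linear slope, is average change per week. The two part company in two ways.

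1. **Amount read as speed.** If both arms follow the same time course but one improves more in total, the slopes differ and the rule reports a difference in speed.
2. **Direction reversed.** If both arms end at the same score but one falls early and then levels off, its later flat weeks pull its fitted slope towards zero. The arm that got there sooner has the shallower slope, and the rule calls it slower.

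This is the only stated comparison of the weekly PHQ-9. If the arms end up similar at three months, the path to that point is what this analysis adds, and there a significant result could point the wrong way.

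**Working it through.** **The plan's own figures.** None is given for the weekly analysis. The stated 130 participants and at least 80% power belong to the primary outcome. They reproduce: 65 per arm, standardised difference 0.5, two-sided 5% (assumed) gives power 0.81. Nothing below changes that.

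**Inputs from the document.** 1:1 allocation of 130, so 65 per arm; weekly PHQ-9 in both arms; group predicts the slope. The number of weekly measurements is not stated. Weeks 0-12 is an assumption, suggested by "TAU will be defined as 12 sessions of face-to-face CBT".

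**Assumed inputs.** Mean at week t = 15 - D(1 - exp(-t/τ))/(1 - exp(-12/τ)), so that D is the fall by week 12. Baseline SD 4.5; slope SD / residual SD of 0.35/2.5 (base), 0.2/2 and 0.5/3; complete data; two-sided 5%.

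**Reversal example: D = 7 in both arms, τ = 2 (B-CBT) v 6 (TAU).** Mean difference, B-CBT minus TAU:

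| Week | 0 | 1 | 2 | 3 | 4 | 5 | 6 | 7 | 8 | 9 | 10 | 11 | 12 |
|---|---|---|---|---|---|---|---|---|---|---|---|---|---|
| Gap | 0 | -1.52 | -2.14 | -2.27 | -2.13 | -1.86 | -1.55 | -1.23 | -0.93 | -0.65 | -0.40 | -0.19 | 0 |

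B-CBT is better at every week between the two ends. The least-squares slope difference is Σ(t - 6)·gap / Σ(t - 6)², with Σ(t - 6)² = 182. Weeks 1-5 contribute 7.60 + 8.56 + 6.81 + 4.26 + 1.86 = 29.09. Weeks 7-11 contribute -(1.23 + 1.86 + 1.95 + 1.60 + 0.95) = -7.59. The sum is 21.5, and 21.5/182 = **+0.118 per week** (slopes -0.438 v -0.556). B-CBT gets the flatter slope.

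**How often this is significant.** With a free intercept per arm and complete data, SE = √[(2/65)(slope SD² + residual SD²/182)].

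- Base: √[(2/65)(0.1225 + 6.25/182)] = 0.069; z = 1.70; about 40% significantly slower.
- 0.2/2: SE 0.044; z = 2.70; about 77%.
- 0.5/3: SE 0.096; z = 1.23; about 23%.

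If group may not shift the intercept, generalised least squares gives differences of +0.101, +0.107 and +0.094, and rates of about 31%, 69% and 16%. The range is therefore 16-77%. The rate of a significant result in the correct direction is about 0% throughout.

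**Other curves ending at the same week-12 score, free intercepts.**

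- Exponential, τ 3 v 6: +0.059; 3 v 5: +0.049; 2 v 4: +0.090; 2 v 8: +0.129. All are labelled slower.
- Exponential at rate 0.6 per week v a straight line, both from 15 to 7: +0.20, z 2.2-3.4 over four other assumed variance sets, 59-93% significantly slower. At rate 0.15: +0.03, z 0.3-0.4, mostly no label.
- S-shaped (logistic, scale 1 week, 7-point fall), centred at week 3 v 9: 0.00; 4 v 9: -0.07; 6 v 9: -0.14. These give no difference, or the correct label.

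The sign follows from the weights (t - 6): a gap concentrated in the first half makes the sooner arm look slower, one in the second half makes it look faster, and a symmetric gap cancels.

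**Amount example: τ = 4 in both arms, falls of 5 v 7 points.** Slopes are -0.377 v -0.528, difference 0.151. With the base variances z = 0.151/0.069 = 2.2, so the rule reports a speed difference in about 58% of trials (62% with a common intercept), although the time course is identical.

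**The case against.** A reader might infer that an arm which improves sooner to the same end point is always labelled slower. The documents do not support that. They give no trajectory, and the S-shaped examples show zero or correctly signed differences.

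Even among exponential curves the result depends on forcing equality at week 12. That forcing gives the τ = 6 arm an eventual fall of 7/(1 - exp(-2)) = 8.1 points against 7.0 for τ = 2. With a common eventual fall of 7 points instead, the slope difference is +0.04 (2 v 6), +0.065 (2 v 4), -0.007 (3 v 6), -0.06 (4 v 8) and -0.12 (6 v 12), so most reversals shrink or vanish. With a common intercept and a negative intercept-slope correlation, mild curvature (rates 0.15 and 0.3 v a straight line) turns the sign to -0.02 and -0.01. These points stand and limit the claim to what can happen.

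Four further points carry weight:

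- **Meaning of faster.** It can ordinarily mean more points lost per week. On that meaning the amount example is not a false positive, since the average slopes truly differ. The objection to the rule is then that it repeats a difference in amount under another name.
- **Power comparison.** Setting the slope test against a week-4 comparison would flatter the latter, because week 4 (gap 2.13) lies next to the peak (week 3, 2.27) of curves chosen for illustration.
- **Trial hypothesis.** It might be inferred that the trial's hypothesis implies equal end points by different paths. Aims and hypotheses says only that B-CBT is no less effective.
- **Linearity.** It is inferred from the description of random slopes. A fuller plan, not shown, could code time differently.

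The last point does not dispose of the matter. The article states a conclusion rule as well as a model, and that rule needs qualifying unless time is coded so that the tested term isolates speed.

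**Conclusion.** The point holds as a limited one. On the plain linear reading, a significant slope difference shows a difference in average weekly change and cannot by itself show faster or slower effects. With early improvement that levels off, the label can be reversed: about 16-77% of trials significantly wrong for time constants 2 v 6 weeks with equal week-12 scores. That figure rests on assumed curves, variances, complete weekly data over weeks 0-12 and two-sided 5%. Under later-separating curves the label can be right or the difference zero.

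The analysis is additional. The three-month ANCOVA is reported separately, so a difference in amount would be visible beside the slope. The primary conclusion and the sample size of 130 do not change. The correction is worth making because the reading is fixed in advance and changing it costs little.

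**What to change.** Model the weekly PHQ-9 with time that allows curvature: week as a categorical factor, or piecewise linear with a knot fixed in advance (week 4, for example), with group-by-time terms and baseline PHQ-9. Replace the conclusion sentence with wording such as: speed of response is judged by a pre-set early-phase contrast (the adjusted group difference at a named early week, or the early-phase slope) with its 95% CI, read together with the end-of-treatment difference. An early difference that has gone by the end of treatment suggests a difference in speed; one that persists or grows suggests a difference in amount.

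If the single linear slope is kept, report it only as a difference in average weekly change, drop the conclusion about faster or slower effects, and state whether group may shift the intercept.

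The cost is wording and a few more parameters, with some loss of efficiency if trajectories are truly linear. No new data are needed, since the weekly PHQ-9 is already collected in both arms.

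### Covariates for the weekly PHQ-9 mixed model, and possibly for the primary ANCOVA, are to be chosen by baseline significance tests, which select on chance imbalance rather than prognostic value.

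*Protocol article*

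**What the plan says.** The section Sample size and statistical analyses of the Protocol article describes two PHQ-9 models.

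- Its first paragraph gives the primary analysis, an ANCOVA "regressing the three-month follow-up PHQ-9 data on the baseline PHQ-9 score and a treatment group indicator". The Abstract repeats this model with no other covariate.
- Its third paragraph adds a supplementary analysis: "we will compare the development of PHQ-9 in the two groups using the weekly measurements in a mixed effects model", with random individual slopes predicted by treatment group. That paragraph closes with the sentence at issue: "Variables with significant variations between groups at baseline are introduced as control variables".

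The sentence does not say which variables are candidates, at what level they are tested, or whether it applies to the mixed model alone or to the ANCOVA as well.

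The section Randomisation and blinding states that randomisation is "at an individual level, stratified by country after eligibility and baseline measurement", "with an allocation ratio of 1:1". It also says that analysts are blinded and that groups carry numbers that do not reveal the treatment.

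**The concern.** When individuals are randomised after their baseline values are recorded, a baseline difference between arms is chance. A small p-value for that difference says nothing about whether the variable predicts PHQ-9. The rule therefore admits a strong predictor and an irrelevant variable with the same probability, and the final model is unknown until baseline data have been compared by coded arm.

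Two things are at stake. One is pre-specification of the mixed model and, if the sentence reaches that far, of the primary ANCOVA. The other is precision. Covariates help when they are prognostic and always included, and a rule driven by imbalance secures neither.

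**Working it through.** **1. The plan's own figure.** Inputs from the sample size paragraph: "A sample size of 130 in two balanced groups" "will yield a power of at least 80" per cent "to detect standardised mean differences above 0.5 on a normally distributed variable". Alpha and sidedness are not stated there; 5% two-sided (one-sided 2.5%) is assumed. With 65 per arm and SD 1:

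- noncentrality = 0.5 × √(65/2) = 2.850
- power = Φ(2.850 − 1.960) = Φ(0.890) = 0.813; the exact noncentral t gives 0.808

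The stated power reproduces. It uses no covariates, so the selection rule does not affect it.

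**2. How often chance adds a covariate.** Assume each candidate is tested at 5% and candidates are independent. P(at least one enters) = 1 − 0.95^k:

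| Candidates k | P(at least one enters) |
|---|---|
| 5 | 23% |
| 8 | 34% |
| 10 | 40% |
| 15 | 54% |

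The range is shown because the plan gives no list. Table 2 collects demographics, current treatment, the diagnostic interview, QIDS-SR16, PHQ-9, treatment preference and expectancy at baseline, so a number in this range is plausible.

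**3. How often a useful covariate enters.** Under randomisation any one variable, prognostic or not, is significant with probability 5%. In simulation the prognostic variable entered in 4.9% to 5.0% of trials. With 65 per arm a difference must reach about 1.98 × √(2/65) = 0.35 SD to qualify, so a smaller imbalance in a strong predictor stays unadjusted.

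**4. What the rule does to the estimate.** This was a simulation of 8,000 trials per setting, with 130 patients and a single-timepoint ANCOVA. Assumptions, none from the documents: baseline PHQ-9 coefficient 0.5, eight independent candidates, one of them prognostic with coefficient 0.3 or 0.5, and the other seven irrelevant.

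| Model | Mean SE (0.3 / 0.5) | Rejection at true difference 0 | Power at 0.5 SD |
|---|---|---|---|
| Baseline PHQ-9 only | 0.152 / 0.152 | 0.054 / 0.046 | 0.90 / 0.90 |
| Selection rule | 0.153 / 0.152 | 0.050 / 0.038 | 0.90 / 0.91 |
| Prognostic covariate always in | 0.143 / 0.125 | 0.053 / 0.053 | 0.93 / 0.98 |

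Analytic check of the first row: √(2/65 × (1 − 0.5²)) = √(0.03077 × 0.75) = 0.152. For the third row: √(0.03077 × 0.66) = 0.143 and √(0.03077 × 0.50) = 0.124.

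Under the rule the estimates vary slightly less than with baseline PHQ-9 alone (empirical SD 0.152 against 0.153, and 0.147 against 0.153), because large imbalances in the predictor are corrected when they occur. The reported SE does not reflect this, so the test is, if anything, conservative (0.038).

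**5. How much an added covariate could bring.** This depends on its overlap with baseline PHQ-9. An independent covariate with correlation 0.4 takes residual variance from 0.75 to 0.59, a 21% fall. QIDS-SR16 measures the same construct as PHQ-9. With an assumed PHQ–QIDS correlation of 0.6 to 0.8 and a QIDS–outcome correlation of 0.4 to 0.5, R² = (r₁² + r₂² − 2r₁r₂r₁₂)/(1 − r₁₂²), with r₁ = 0.5. At r₂ = 0.5 and r₁₂ = 0.6 this is 0.3125, so residual variance is 0.6875, an 8% fall. At r₂ = 0.4 and r₁₂ = 0.8 it is 0.25, so there is no fall.

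**The case against.** The strongest reply is about scope. The primary model is written out in full, with two terms, in its own paragraph and again in the Abstract. The sentence on control variables closes a different paragraph, on a supplementary slope analysis that has no margin. A reader might infer that the rule decides whether the primary comparison meets the 0.5 SD limit. The documents do not establish that; it follows only if the sentence also governs the ANCOVA, which they leave unclear. For the same reason the ANCOVA simulation does not measure the rule's effect on the slope model.

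The second reply is about size. A reader might set the rule against a model that always includes a good extra predictor and call the gap the cost of the rule. With an independent covariate of correlation 0.4, the variance ratio is 0.75/0.59 = 1.27. That ratio measures the benefit of the assumed predictor. It would be missed equally if the sentence were simply deleted. Against baseline PHQ-9 alone, the rule changes the SE by at most about 0.001 SD. Nor is type I error inflated. Both replies stand.

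Third, analysts are blinded and a candidate list may sit in an analysis plan that is not shown. Blinding limits steering towards one arm, and a missing list is not the point here. Neither answers the objection to the criterion itself, which the article states outright: entry still depends on the coded allocation, and significance of imbalance still says nothing about prognosis.

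**Conclusion.** The point holds as a defect in a stated rule, with modest consequences. The rule selects covariates on chance. At an assumed 5% level with independent candidates, something enters by luck in roughly a quarter to a half of trials, and a chosen prognostic variable in about one in twenty. The PHQ-9 mixed model, and possibly the primary ANCOVA, is therefore not fixed in advance, and nothing is gained in reported precision.

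The documents do not support saying that the rule endangers the non-inferiority conclusion, the false-positive rate or the planned power. The primary model already carries baseline PHQ-9, probably its most useful covariate, so any forgone precision concerns further covariates only. Its size is illustrative because the documents give no correlations.

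**What to change.** Delete the sentence. In its place:

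- State that the primary ANCOVA adjusts for baseline PHQ-9 whatever the observed balance.
- Name in advance a short list of any further baseline covariates expected to predict PHQ-9, drawn from data already collected. Current treatment and patient expectancy are examples; QIDS-SR16 may add little beyond PHQ-9.
- Say which PHQ-9 models the list covers: the ANCOVA, the weekly mixed model, or both.
- Confine any adjustment for observed imbalance to a labelled sensitivity analysis.

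Deletion alone restores a fixed model; only the named covariates can add precision. The change needs wording only, with no new data and no change to the sample size, and should be settled before anyone compares baseline data by coded arm.
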